### Who will take informed consent?

The study participants (children and guardians) will receive written information about the purpose and procedure of the study and about possible advantages and disadvantages of participation. They will be informed that participation in the study is entirely voluntary, and that participation can be terminated at any time without giving reasons. Additionally, all participants will be informed about their rights regarding data storage, data protection and data deletion. Informed consent will be obtained from all guardians as well as children in child-friendly language prior to screening at T0. Only individuals who provide informed consent and child assent can participate in the study.

### Intervention description

The intervention consists of two components: the Aumio app and the parent-centred email psychoeducation module. Both are made available to participants. Aumio is a smartphone application designed to provide easily accessible health interventions for children and to promote healthy sleep and strengthen children’s mental health. It focuses on children’s sleep, relaxation, concentration and emotions. In the sleep module, Aumio offers a variety of audio stories, fantasy journeys and sounds for falling asleep to make going to bed in the evening as relaxing as possible for children. In addition, psychoeducation and the playful learning of relaxation techniques by means of meditations and dream journeys are integrated into the Aumio app. The meditation techniques are taught in a child-friendly way and made easily accessible for children. The exercises and stories are based on cognitive-behavioral techniques such as autogenic training or progressive muscle relaxation. The meditations and dream journeys for falling asleep have a duration between 5 and 20 minutes. In the intervention, families are advised to use the Aumio app at least twice a week in the evening, before bedtime. However, participants are encouraged to integrate the Aumio app into their daily routine in a manner that is suitable for them.

In addition, the parent-centred email psychoeducation module accompanies the use of the Aumio app and is emailed to the guardians once a week. The course addresses various aspects of children’s sleep to provide guardians with an understanding of child sleep and associated challenges. Each week focuses on a specific topic that covers relevant aspects of children’s sleep and sleep habits. First, the importance of good sleep quality for child development is discussed. Then, falling asleep is addressed by teaching the creation and establishment of bedtime routines and highlighting the importance of a comfortable sleep environment. Potential obstacles are also addressed. The parents are also taught how to help their children fall asleep on their own and how to make the process of accompanying their child to sleep less stressful. The course then tackles issues with staying asleep and provides strategies to support the child in falling back asleep after a nighttime awakening. Last, the course discusses how the child’s daytime activities can influence their sleep. For each topic, practical tips for implementing the concepts in daily life are provided alongside the theoretical explanations. The knowledge learned can be tested weekly in a small quiz in the Aumio app. In addition, the most important content is compiled in a child-friendly way and sent as a playfully designed info sheet as an attachment to the e-mail.

### Criteria for discontinuing or modifying allocated interventions

Participants can discontinue their use of the Aumio app, stop receiving the parent-centred email psychoeducation module, and consequently withdraw from the study at any time by uninstalling the app from their mobile devices and opting out of the email list. The intervention does not require contact with the study team.

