## Abstract

Sleep problems are widespread among children and can have a negative impact on their development, everyday functioning and pose an additional burden on the parents. While there are numerous apps designed to improve children’s sleep and help them fall asleep, little data are available regarding the feasibility, acceptability and efficacy. The purpose of this study is to conduct an initial analysis of the feasibility and acceptability of the Aumio app and an email psychoeducational module as well as preliminary efficacy on child’s sleep quality and the associated factors well-being and parental stress. This research project is designed as a single-group pre-post design for a sample of 456 guardian-child dyads, with children aged 6–12 years. Participants will be recruited through the Aumio app as well as through advertisements in pediatric clinics and online. During the 12-week intervention, participants will be provided with the Aumio app and the parent-centred email psychoeducation module. At the beginning of the intervention and before the first app use (T0), six weeks after the first app use (T1), and immediately following the conclusion of the 12-week intervention (T2), the feasibility, acceptability and preliminary efficacy on children’s sleep and health-related quality of life as well as parental stress will be examined. The study will examine the association between the intensity of the Aumio app use and the endpoints to improve feasibility and acceptability by synthesizing recommendations for use. This pilot study can provide important insights into an app targeting child’s sleep problems in naturalistic, uncontrolled settings. Through this study, the existing research gap regarding app-based interventions for improving infant sleep will be addressed. Results will stimulate further development and research in the area of evidence-based mobile health interventions for children and their parents.

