### Trial design and study setting and participant timeline

The present research project is designed as a one-group pre-post pilot study. As this trial is the first larger scale pilot trial on the feasibility and acceptability as well as the first trial on the preliminary efficacy of the app on sleep quality and the parent module, randomization, control groups, and blinding do not apply to the study design of this trial. The study is a single study conducted in the naturalistic setting of the app, meaning it was conducted exclusively in-app and within a German-speaking population. After consenting to participate in this study, the participants will be provided a 12-months free access to the Aumio app and receive the parent-centred email psychoeducation module at weekly intervals.

Once participants agree to the conditions of participation and meet the inclusion criteria, guardians are directed to the first assessment (T0). At T0, at the beginning of the intervention and before the first app use, data on sociodemographic characteristics and relevant covariates and the outcomes will be collected. After completing the first survey T0, participants are provided with free access to the Aumio app for one year and receive the parent-centred email psychoeducation module once a week. The intervention duration is set at twelve weeks. Six weeks after the intervention start and the first app use, the second measurement point (T1) takes place, where primary and secondary outcomes are assessed. Immediately following the conclusion of the 12-week intervention, the third measurement point (T2) is conducted, comparable to the T1 assessment (Fig 1).

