### Sample size

With regard to the required sample size, two factors were considered in the present study: The Aumio app for the children and the parent training. For the parent training, we first considered effects on child outcomes as a basis for sample size calculation. An average effect size of parent training of d = 0.20 was found in a meta-analysis on the effectiveness of family-based prevention interventions [31]. An average effect size of d = 0.21 of universal prevention programs was found in a meta-analysis on German-language effectiveness research [32]. Based on these findings, with an assumed power of.90, an alpha error level of.05, and an effect size of.21, a required sample size of 196 was calculated using the software g*Power [33].

Considering the drop-out rate (DOR) observed in the unpublished master’s theses on the Aumio app, this was also considered for sample calculation. In one of the most recent master’s theses on the effectiveness of the Aumio app, a drop out of 57.14% was found in the treatment group. Based on an expected DOR of 0.57, the number of cases is multiplied by the correction factor 1/(1-DOR) [34]. If the previously calculated sample size is increased by the expected DOR, a final required sample size of 456 is needed.

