### Methods in analysis to handle protocol non-adherence and any statistical methods to handle missing data

Multiple imputation methods are used to estimate missing data. The trial is supervised by the evaluation team, which is the contact for reporting of any adverse event.

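### Stopping both the app and the e-mail course counts as leaving the study, and T1 and T2 have no single start date, so survey outcomes risk describing mainly continuing users

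*Protocol article*

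**What the plan says.** The section on criteria for discontinuing or modifying interventions describes one exit route. Families may stop the app, stop the e-mails and "consequently withdraw from the study at any time by uninstalling the app from their mobile devices and opting out of the email list". No section says that families who stop are still invited to T1 or T2.

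The assessment dates are worded in several ways:

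- The Abstract places follow-up "six weeks after the first app use (T1), and immediately following the conclusion of the 12-week intervention (T2").
- The trial design section says "Six weeks after the intervention start and the first app use, the second measurement point (T1) takes place", as if these two starts were one date. T2 follows the end of the 12-week intervention. App access and weekly e-mails both begin after T0.
- The Objectives place the first feasibility survey six weeks after app use begins and also at the midpoint of the e-mail module. They count 6 and 12 weeks from the start of app use for the child outcomes, but 12 weeks from the start of the e-mail programme for parenting stress.

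App use is advised at least twice weekly but left to the family, and no reminders are sent (sections on the intervention and on adherence).

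The sample size section plans for heavy loss, based on an earlier thesis in which "a drop out of 57.14% was found in the treatment group". The stated remedy is "Multiple imputation methods are used to estimate missing data".

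**The concern.** Whether a family stays in the data may depend on whether it stays with the product. If stopping the intervention ends survey contact, T1 and T2 scores come mainly from families who kept using it. This affects two kinds of result.

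The first is the pre-post change in sleep, quality of life and parenting stress. The study has no control arm ("The present research project is designed as a one-group pre-post pilot study"), so the mean change is the whole efficacy result, and selective loss enters it directly.

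The second is acceptability, which belongs to the primary outcome and is collected by survey at T1 and T2. Families who gave up are well placed to say what made the app hard to use, and they are the ones most likely to go unasked. The dropout rate is itself a feasibility outcome, and it is hard to interpret if quitting the product and quitting the study are one event.

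The dates add a separate problem. With several clocks in use, the interval between assessments depends on when a family first opens the app.

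**Working it through.** **1. The plan's own figures.** Inputs from the sample size section: "with an assumed power of.90, an alpha error level of.05, and an effect size of.21", and "a required sample size of 196 was calculated using the software g*Power". A one-sided paired t-test with d = 0.21 and alpha 0.05 gives n = 196 (power 0.9006), so the figure reproduces. The article does not state whether the test is one-sided, which does not affect this point. Inflation for dropout: 196 / (1 − 0.57) = 196 / 0.43 = 455.8, rounded up to 456. Expected without outcome data: 456 × 0.57 = 259.9, about 260. Expected with data: 456 × 0.43 = 196.1, about 196.

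**2. The dates.** Take a family whose e-mails start in week 0 and who first opens the app three weeks later.

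- T1, six weeks after first use: 3 + 6 = week 9.
- T2, end of the 12-week intervention: week 12.
- T2 on the Objectives' clock for child outcomes, 12 weeks after first use: 3 + 12 = week 15.
- Parenting stress, 12 weeks after the e-mails start: week 12.

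T1 and T2 are then three weeks apart instead of six, or one T2 survey has two due dates. The clocks agree only if the app is first opened when the intervention starts. A family that never opens it has no T1 date on the first-use clock.

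**3. Possible size of the selection effect.** Assume that the observed 43% improve by 0.21 SD, that the missing 57% improve by k × 0.21 SD, and that imputation gives the missing the stayers' change. Then:

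- true change over all enrolled = 0.43 × 0.21 + 0.57 × k × 0.21
- overstatement = 0.21 − true change = 0.57 × (1 − k) × 0.21

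| k | True change (SD) | Overstatement (SD) |
|---|---|---|
| 1 | 0.21 | 0.00 |
| 0.75 | 0.18 | 0.03 |
| 0.5 | 0.15 | 0.06 |
| 0.25 | 0.12 | 0.09 |
| 0 | 0.09 | 0.12 |
| 1.5 | 0.27 | −0.06 |

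The row k = 0.5 also covers the case where half of the missing families do not change and the other half change like stayers.

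**4. Whether imputation repairs it.** A simulation used 456 dyads, 57% missing at T2, a T0–T2 correlation of 0.5, a true mean change of 0.09 SD, normal-model multiple imputation and 500 runs. Mean estimates were:

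| Reason for dropout | Completers | Imputed from T0 | Imputed from T0 and logged use |
|---|---|---|---|
| Unrelated to change | 0.093 | 0.093 | 0.093 |
| Use drives both staying and improving | 0.185 | 0.187 | 0.093 |
| Depends directly on the unseen change | 0.288 | 0.288 | 0.289 |
| Improvers leave | −0.116 | −0.116 | −0.117 |

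If app use explains the link between staying and improving, imputation that includes it removes the bias. If families leave because of an outcome that nobody recorded, no imputation from the available data removes it. Only collecting those outcomes does.

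**The case against.** Several stronger readings are tempting, and the article does not support them.

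- *Uninstalling alone is withdrawal.* The text joins uninstalling with opting out of the e-mails. A family that drops the app but keeps the e-mails, or simply stops using the app, is not described as withdrawn.
- *Outcome collection depends on the app.* The questionnaires run on an external survey server, and a 30 euro voucher is paid for completing T2 with no condition on app use. The trial design section does say that the study runs wholly inside the app. The two statements conflict, so loss of surveys on uninstalling is not established.
- *Non-starters vanish from the feasibility result.* User numbers, dropout and usage are feasibility outcomes, and use is logged separately from the questionnaires. Non-starters still count there. What is at risk is the survey-based material.
- *The change is biased upward, 2.3-fold.* That ratio (0.21 / 0.09) is the single case in which every missing family has zero change. The 57% is a planning rate from one thesis and includes whatever ordinary non-response occurred there. The bias is nil or reversed under other reasons for leaving, and families whose child now sleeps well may also stop.
- *The imputation plan is deficient.* Variables, assumptions and sensitivity analyses are commonly left to an analysis plan, which is not shown. The brevity of that sentence is no fault in itself.

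Two further points have weight. Users recruited in the app enrol just before first use, so long delays may be uncommon. The efficacy outcomes are secondary, and the Discussion already rejects a causal reading, although it does not mention attrition among the limitations.

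What survives is narrower. The text merges stopping both components with leaving the study, promises no survey to those who stop, and gives T1 and T2 inconsistent origins. These are matters of conduct, and a later analysis plan cannot recover outcomes that were never collected.

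**Conclusion.** The point holds as a risk created by the conduct rules, not as a demonstrated bias. Followed as written, the plan may lose survey outcomes selectively by engagement, at a loss that it expects to reach about 260 of 456 dyads. If leavers improve by between none and all of the stayers' 0.21 SD, the overstatement is 0 to 0.12 SD, and the top of that range exceeds half of the planned effect (0.12 / 0.21 = 0.57). This rests on three assumptions: the planning dropout rate holds, stayers reach the planned effect, and imputation gives leavers the stayers' change. Neither the direction nor the size can be read from the article. The inconsistency in dates needs none of these assumptions and stands on the text. The change is worth making because it is cheap and has to be made before the data are collected.

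**What to change.** 1. In the section on discontinuing interventions, separate stopping the intervention from withdrawing from the study. Keep sending T1 and T2 survey links to families who stop either or both components, unless they withdraw consent. Send the links from a list separate from the course e-mails, so that opting out of the course does not end survey contact. Report stopping the app, stopping the e-mails and leaving the study as separate counts.
2. Reconcile the statement that the study runs only inside the app with the use of an external survey server.
3. Date T1 and T2 at 6 and 12 weeks after T0 for every enrolled dyad, including those who never open the app. Use that wording in the Abstract, the Objectives and the trial design section.
4. Optionally, include logged app use in the imputation model. For families still missing, add a sensitivity analysis that imputes no change from T0 or applies a delta shift.

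The cost is revised wording, some extra automatic survey e-mails and possibly a notification to the ethics committee, since the change alters what families are told about withdrawal. The resulting estimate may be less favourable.

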### Strategies to improve adherence to interventions

The use of Aumio is entirely app based, and the meditations and dream journeys last between 5 and 20 minutes. Thus, the effort required to engage with the app can be considered minimal. As the naturalistic context of the study is among users of the Aumio app, the app functions are not altered for the study. Consequently, no reminders of app use will be used.

### Outcomes

#### Primary, feasibility outcome.

Feasibility will be assessed by the number of users, dropout rates, and usage patterns (e.g., number of audio content played). Usage behavior of the parent-centred email psychoeducation module will be assessed weekly using a content related quiz question in the Aumio app. The recruitment process will further be examined by analysing the study outreach method and its consequences on participant recruitment.

The acceptability of the Aumio app and the parent-centred email psychoeducation module will be assessed both quantitatively and qualitatively by examining the user’s satisfaction. The questions are derived from a study by Hiscock et al. [13], which examined the effects of a digital sleep intervention on child sleep and psychosocial outcomes of children and their caregivers. Satisfaction is assessed on 5-point Likert scale (1 = totally disagree/very unsatisfied, 5 = totally agree/very satisfied) generally and by specific factors, including satisfaction with the use of the product (“The app was easy to use”; “The e-mail course was understandable.”), the information provided (“The amount of information in the app was just right.”; “I was satisfied with the content provided by the app.”; “The amount of information in the e-mail course was just right.”; “I was pleased with the strategies the email course provided for my child’s sleep problem”; “I would have preferred to have a personal contact instead of the e-mail course to explain the strategies and their application.”), the feeling of safety (“I felt safe using the app.”; I felt safe participating in the email course.”), the subjective perception of improvement in the child’s sleep (“Using the app has helped my child to fall asleep.”; “Taking part in the e-mail course has helped my child to fall asleep better.”), and the intention to continue using the product in the future (“I would like to continue using the e-mail course in the future.; “I would like to use the app in the future.”). Likelyhood of recommendation to other parents (“How likely is it that you will recommend the Aumio app to other parents you know?”, “How likely is it that you will recommend the e-mail course to other parents you know?”) will be assessed using a 10-point Likert scale (1 = unlikely, 10 = highly likely). Quantitative data will be further supplemented by qualitative data on helpful content (“What has helped you and your child the most with the Aumio app?”, “What did you and your child find particularly helpful about the email course?”), ideas for improvement (“What would you change to improve the Aumio app?”, “What would you change to improve the email course?”), as well as moments when users experienced difficulty using the app (“When did you find it difficult to use the Aumio app?”). Additionally, we will assess changes in sleep duration (“Has your child’s sleep duration changed with the use of Aumio and the e-mail course?”) and whether parents sought advice from their local paediatrician regarding sleep problems (“While using the Aumio app and email course, did you contact your local paediatrician for more information on how to help your child sleep?”).

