The secondary, user-centred hypothesis refer to comparisons of endpoint scores pre app use, at the same time points as the feasibility survey. We hypothesize that 6 weeks and 12 weeks after the start of the app use, children’s sleep quality will be significantly increased (secondary, child-centred endpoint) and health-related quality of life will be significantly higher (secondary, child-centred endpoint). Furthermore, we hypothesize that parenting stress will be significantly reduced 12 weeks after the start of the use of the email psychoeducational program (secondary, parent-centred endpoint). Exploratory analyses will also be conducted to determine to what extent usage behavior influences the effects on primary and secondary outcomes.

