#### Data management.

The data of the questionnaires and the data of the app are collected separately, and the assignment is only possible via an assignment list, which are exclusively encrypted and password-protected and stored locally in separate folders. The hard drive will be located at Freie Universität Berlin.

No sensitive, personal data is collected via the Aumio app, but only data that has a technical background (e.g., device identification and information, language, etc.) and represents user behaviour (e.g., number and duration of app use). Furthermore, the data is only collected under a pseudonym, which is created by the participants themselves at T0. The pseudonym consists of the first two letters of the participant’s first name, the last two digits of their current ZIP code, and the first two letters of the name of the participant’s first child.

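### Use of the e-mail module, part of the primary feasibility outcome, is measured by a content quiz inside the app, which cannot tell readers from non-readers of the e-mails

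*Protocol article*

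**What the plan says.** Under Objectives, the primary hypothesis covers feasibility and acceptability of two components: the app for the child and the e-mail course for the guardian.

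The section on the primary, feasibility outcome states how use of the second component is captured: "Usage behavior of the parent-centred email psychoeducation module will be assessed weekly using a content related quiz question in the Aumio app".

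The Intervention description gives the delivery route, "the parent-centred email psychoeducation module accompanies the use of the Aumio app and is emailed to the guardians once a week", and describes the quiz in permissive terms: "The knowledge learned can be tested weekly in a small quiz in the Aumio app".

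Other places that bear on the measure:
- Strategies to improve adherence: "Consequently, no reminders of app use will be used".
- Data management: "The data of the questionnaires and the data of the app are collected separately". Data from a mailing system are not mentioned.
- The listed survey items on the e-mail course cover ease of understanding, amount of content ("The amount of information in the e-mail course was just right"), strategies, preference for personal contact, safety, perceived help, intention to continue, recommendation and open comments. None asks how many e-mails were read.
- Missing data: "Multiple imputation methods are used to estimate missing data". Nothing is said about an unanswered quiz.

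**The concern.** The course reaches guardians through one channel and its use is recorded in another. The article describes no step that makes a guardian open the app in order to read an e-mail, and none that obliges anyone to answer the quiz. The quiz is also a knowledge question, which is a different construct from having received or read the material.

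The stake is how the pilot is read. The Discussion says the results will inform a later randomised trial and changes to the intervention. If few quizzes are answered, the sponsor could conclude that parents do not use the course when only the quiz was unpopular. If many are answered by guardians who did not read the e-mails, the opposite mistake follows. The usage figures of the two components will also tend to move together because of how one of them is measured, whatever guardians actually do with the e-mails.

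**Working it through.** The plan gives no figure for e-mail use or quiz answering, so there is none to reproduce. The check is a reading of the relevant sections together, followed by one identity.

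**Step 1. What each source can record.**

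| Guardian's behaviour in a week | Quiz record | E-mail items listed for the survey |
|---|---|---|
| Reads e-mail, answers quiz | Yes | Opinion of course |
| Reads e-mail, skips quiz or does not open app | None | Opinion of course |
| Does not read, answers quiz | Yes | Opinion of course |
| Does not read, no quiz | None | Opinion of course |

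Rows 1 and 3 leave the same usage record, and so do rows 2 and 4. None of the listed e-mail items separates the rows, because they ask for opinion and not for amount read.

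**Step 2. Direction of the error.** Let *r* be the share of guardians who read a given week's e-mail, *q* the share of readers who answer the quiz, and *s* the share of non-readers who answer it. Then:

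- quiz-based use = *r q* + (1 − *r*) *s*
- quiz-based use − true use = (1 − *r*) *s* − *r* (1 − *q*)

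The first term is non-readers who answer; the second is readers who do not. Use is understated when the second term is larger and overstated when the first is. The article gives none of *r*, *q* or *s*, so neither sign nor size can be derived from it.

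**Step 3. Dependence on app use.** The quiz sits in the app. If *a* is the share of families opening the app that week, then quiz-based use cannot exceed *a*, whatever *r* is. A guardian who stops opening the app but stays on the mailing list produces no further record of course use. The section on discontinuing names uninstalling the app and opting out of the e-mails as two separate actions, so this pattern can occur.

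**Step 4. What a survey item could add.** The course runs weekly for 12 weeks, with T1 at week 6 and T2 at the end, so each interval holds 12 / 2 = 6 e-mails. That fixes the 0 to 6 scale proposed below. The Sample size section expects a dropout of 0.57: 196 / (1 − 0.57) = 455.8, rounded to 456. Of 456 enrolled, about 196 are thus expected to remain and about 456 − 196 = 260 to be lost. A T1/T2 item will miss many of these, whereas the weekly quiz can record activity before they leave.

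**The case against.** **The quiz is a reasonable engagement measure.** It is described together with the course, it runs weekly, and it can collect data before people drop out. The outcome section speaks of usage behaviour, not of e-mails read, and feasibility is only summarised descriptively. This stands as a reason to keep the quiz. It does not make quiz answers a measure of whether the e-mails are used.

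**The article is condensed.** The full protocol may list mailing counts or further items, and their absence here would not by itself be a finding. That is right, and the point does not rest on it. It rests on the measure the article does state, which does not fit what it is meant to capture.

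**The quiz is never called optional.** Correct; that is read from the wording that knowledge can be tested there, and from the absence of any described obligation or reminder.

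Three stronger readings are tempting and are not supported:
- *Guardians who skip the quiz are counted as non-users.* The article gives no scoring rule for an unanswered quiz, and its general statement on multiple imputation leaves the treatment open. It is exact to say only that they cannot be told apart from non-readers.
- *Use of the course is understated.* Step 2 shows that this depends on rates the article does not give.
- *Exposure in the parenting-stress analysis is misclassified.* The hypothesis is timed from the start of the course ("parenting stress will be significantly reduced 12 weeks after the start of the use of the email psychoeducational program"), but all participants are sent the course after T0 and change is analysed by repeated measures ANOVA. The four-level and continuous intensity analyses are defined on app use. Objectives also mentions exploratory work on usage behaviour in general terms, but no stated analysis uses a quiz-based exposure.

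**Conclusion.** The concern holds as a mismatch between construct and measure within the primary feasibility outcome. As written, a reader who skips the quiz and a non-reader look the same, an answered quiz does not establish reading, and recorded course use is capped by app use. The error may go either way and its size cannot be computed from the article.

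This rests on two readings: that the quiz is voluntary, and that the stated quiz is the usage measure actually intended. If the full protocol also records e-mails read or clicked, the point reduces to naming the quiz correctly. It does not affect the planned tests of sleep, quality of life or parenting stress. It limits what can be concluded about the feasibility of one of the two components, and it is worth correcting because the correction is cheap.

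**What to change.** 1. Keep the weekly quiz, but report it as quiz completion and knowledge, not as use of the e-mail course. Change the sentence in the outcome section accordingly.
2. Add one item at T1 and one at T2: how many of the weekly e-mails of the last six weeks did you read (0 to 6)?
3. Report delivery, click and opt-out counts from the mailing system where these are already available.
4. Present the three sources side by side, with the number of guardians contributing to each.

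The cost is one short question at two existing surveys and a change of wording. The design and the intervention stay as they are. The item has limits: it is self-reported, so over-reporting is possible; it asks for six weeks of recall; and it will be missing for those who leave before T1 or T2, with 57% dropout expected. It should therefore be read with the quiz and the mailing counts and should not replace them.
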